**DEVIATION OF FINAL MANUSCRIPT FROM PROTOCOL SUBMITTED TO REB**

***While the MAS of increased tone was collected in study subjects, this information was not included in the final manuscript as it became clear during assessments that MAS was not a valid measure in paratonia due to its fluctuating nature (Waardenberg H, Elvers W, Van Vechgel F, Oostendorp R. Can paratonia be measured reliably? Evaluation of the reliability of a visual analogue scale and the modified tonus sclae of Ashworth for measuring paratonia. Nederlands Tijdschrift voor Fysiotherapie 1999;102:30-35).***

1. **Time to Perform Care:** Time to perform hygiene and dressing will be determined with video recording analysis prior to and following injections. Specifically, time in minutes to perform individual goals (dressing (upper body), cleaning under arm, cleaning palm, cutting nail, all tasks involved in the Carer Burden Scale) will be recorded by study nurse observing the professional caregiver and averaged over 2 days during assessments.

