**Proposal**

**Objectives:**

Perform a pilot study to assess the impact of Botulinum toxin type A on muscle tone, time to provide care, and carer burden in individuals who are cognitively impaired and fully dependent.

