**Pilot study objectives**

*Primary Objective*:

1. Confirm proof of principle that paratonic rigidity and its consequences can be reduced with Botulinum toxin injections resulting in reduced caregiver burden.

*Secondary Objectives:*

1. Determine optimal time points for evaluation of efficacy in this patient
   population and whether this time period is sufficient for washout of Botulinum toxin effect
2. Determine most salient and sensitive outcome measures
3. Identify obstacles in data gathering
4. Determine feasibility of battery of assessments in this pilot study that will eventually be used in a future phase III study

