**DEVIATION OF FINAL PROTOCOL FROM PROTOCOL SUBMITTED TO REB**

***As cutting fingernails was not consistently part of daily morning care in this population, it was omitted from the assessments. Since we included both left and right limbs, cleaning under the armpit and cleaning under the palm was scored for each side. As such, the total achievable score was 20. This was an oversite in the original protocol and became clear that scoring modification was required once study began.***

*Secondary Outcomes*

1. **Tone:** Tone will be assessed by the study co-ordinator using the Modified Ashworth Scale (MAS) of increased tone (7, 20). This is a 6 point scale grading the level of resistance encountered during manual passive stretching with 0=No increase in muscle tone, 1=slight increase in muscle tone, manifested by a catch and release, or by minimal resistance at the end of the range of motion when the affected part(s) is moved in flexion or extension, 2=Slight increase in muscle tone, manifested by a catch, followed by minimal resistance throughout the remainder (less than half) of the range of motion, 3=More marked increase in muscle tone through most of ROM, but affected part(s) easily moved, 4=Considerable increase in muscle tone, passive movement difficult, 5=Affected parts rigid in flexion and extension. Tone of the fingers, elbow, wrist, and shoulder abduction (depending on the muscles affected and injected) at baseline and after active and sham treatments, will be compared. A clinically significant response to treatment will be defined as at least a one point improvement from baseline in scores for muscle tone in the wrist and fingers (21).

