**DEVIATION OF FINAL MANUSCRIPT FROM PROTOCOL SUBMITTED TO REB**

***This data was collected but it became clear that this method of determining time it takes to accomplish morning routine was not feasible. There were different people performing morning care at each assessment in different ways and with variable efficiency despite trying to ensure prior to emrolment that this was uniform. For “time to perform morning care” to become a valid measure it would be necessary to standardize the protocol for administering care and by the same individual. As this study was a pilot study also looking at feasibility, we recognized that the way we collected this did not provide meaningful and valid data and chose to omit from our reporting. A future study on a larger scale (if performed) would need to consider these factors and record the time variable in a different way.***

1. **Visual Analogue Scale:** A caregiver burden visual analogue scale (VAS) will be completed by the professional caregiver caring for the patient in order to assess perception of ease of caregiving (16). A VAS will be used because it has been found to be valid in capturing subjective perceptions of health-related quality of life and other qualitative health outcomes (24). The VAS consists of a 100 mm line with anchors of 0 “giving care to the residents is very difficult” and 100 “giving care to the residents is very easy”.
2. **Global Assessment**: Overall response to treatment will be evaluated by the study investigator and by the professional caregiver caring for the patient using the global assessment scale (26) at each follow-up visit. A score of -4 indicates very marked worsening, 0 no change, and +4 very marked improvement.
3. **Pain:** As patients with advanced dementia are not able to express their experience of pain, a surrogate measure, the Pain Assessment in Advanced Dementia (PAINAD) Scale (25) will be used by the study nurse at each assessment time point to objectively evaluate correlates of pain and determine whether treatment with Botulinum toxin reduces the discomfort experienced during morning care. The PAINAD scale consists of 5 items (breathing, negative vocalization, facial expression, body language, and consolability) scored on a 0-2 point scale and then summed to arrive at a total score. The score will be averaged over 2 days

*Qualitative Assessments*

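### Muscle tone and time to provide care, two of the three effects in the objective, were collected and then left out of reporting, with the timing of that decision unstated

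*Protocol*

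**What the plan says.** The Protocol's Objectives section sets out to "assess the impact of Botulinum toxin type A on muscle tone, time to provide care, and carer burden". The primary pilot objective has two linked parts: that botulinum toxin lessens paratonic rigidity and its consequences, and that caregiver burden falls as a result. One secondary pilot objective is to "Determine most salient and sensitive outcome measures".

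Under Secondary Outcomes there are five quantitative measures: tone by MAS, time to perform care, a caregiver visual analogue scale (VAS), a Global Assessment, and pain by PAINAD. For tone the text reads "Tone will be assessed by the study co-ordinator using the Modified Ashworth Scale (MAS) of increased tone (7, 20", the figures being reference numbers. Joints are assessed according to the muscles affected and injected, and response is defined as "at least a one point improvement from baseline in scores for muscle tone in the wrist and fingers (21".

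Two deviation notes follow. On MAS: "While the MAS of increased tone was collected in study subjects, this information was not included in the final manuscript", because "it became clear during assessments that MAS was not a valid measure in paratonia due to its fluctuating nature", with a 1999 reliability study as the cited support. On time: the data were collected, but care was given by different people at each assessment, in different ways and at different speeds, so the authors "chose to omit from our reporting".

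The Statistical Analysis section plans mixed models for the quantitative outcomes, with the patient/caregiver dyad as random effect.

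**The concern.** Leaving out a prespecified outcome once its data exist opens the way to selective reporting. A reader cannot tell an outcome dropped because it was badly measured from one dropped because of what it showed, unless the timing of the decision and the data are given.

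The particular losses matter here too. MAS is the only planned quantitative tone outcome. The Paratonia Assessment Instrument is described only for eligibility, and the videos document posture and skin. Without MAS, the rigidity part of the primary objective has no reported tone measurement behind it. The aim of finding the most sensitive measures also needs results from the measures that did badly as well as those that did well.

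**Working it through.** There is no stated figure to reproduce. The check is a count followed by a comparison of sections.

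**Count**
- Effects in the objective: tone, time, carer burden = 3. Omitted: tone, time = 2. Share omitted: 2/3.
- Quantitative secondary outcomes: MAS, time, VAS, Global Assessment, PAINAD = 5. Omitted: MAS, time = 2. Share omitted: 2/5.

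**The reason given for MAS**
- The Tone item cites references 7 and 20 beside the choice of MAS.
- Reference 20 in the reference list is a 1999 study asking whether paratonia can be measured reliably with a VAS or the modified Ashworth scale.
- The deviation note cites that same study in support of dropping the scale.
- So the question of MAS reliability in paratonia was known when the scale was chosen. Experience during the trial may have made it more pressing, but did not raise it for the first time.

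**The reason given for time**

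The stated problem is a change of carer, method and efficiency between assessments. How far it reaches each measure depends on the rater:

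| Measure | Rater, per Protocol | Exposure to changing carers | Carer-variation note |
| --- | --- | --- | --- |
| Time to perform care | Study nurse timing the carer | Direct | Yes, and omitted |
| Caregiver VAS | Professional caregiver | Direct | None |
| Global Assessment, caregiver rating | Professional caregiver | Direct | None |
| Global Assessment, investigator rating | Study investigator | Indirect at most | None |
| Carer Burden Scale (primary) | Blinded study nurse, on the tasks that were to be timed | Less direct | None |
| PAINAD | Study nurse, for discomfort in morning care | Less direct | None |

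The reason is therefore applied selectively, most clearly with respect to the VAS and the caregiver's Global Assessment.

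**The dyad random effect**

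The treatment effect is a change from injection to 6 weeks later in each cycle. A random effect for the patient/caregiver dyad presumes that the same pair is observed throughout. If the carer at week 0 differs from the carer at week 6, the change contains (carer at week 6 minus carer at week 0), which does not cancel and which a single dyad term does not absorb. The time note thus also weakens the model planned for the retained outcomes.

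**Does noise justify omission?**

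In a randomised, blinded crossover, fluctuating tone and changing carers mainly add variability, provided that carer changes are unrelated to treatment. That is a reason for wide intervals and a caveat. It does not require that the results be left out.

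**Secondary point: the response rule**

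The joints assessed include elbow and shoulder, depending on the muscles injected, but response counts only wrist and fingers. Under that wording, a patient injected only at elbow or shoulder could respond only through change at joints that were not injected.

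**The case against.** The strongest reply is that the authors did what an honest pilot should do. They disclosed both omissions with reasons and kept the primary outcome. The time note names the obstacle and says what a later study would have to standardise, which already goes some way towards the objectives on obstacles and feasibility. This stands. Of the secondary pilot objectives, only the one on sensitive measures clearly lacks its data.

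Four stronger readings are tempting, and the Protocol does not support them:

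- A reader might infer that results drove the omissions. Nothing says so. The MAS note places the realisation during assessments, and neither note says whether the decision preceded unblinding.
- A reader might infer that the Protocol contradicts both reasons. Nothing contradicts the statement that carers changed. For MAS, citing one study twice shows that the question was known. It does not show what the study found, and the note can be read as field experience later tied to known literature.
- A reader might infer that changing carers undermine the Carer Burden Scale as much as the timings. That scale is rated by a blinded nurse in five grades of difficulty, and variable efficiency bears on it less directly than on elapsed minutes.
- A reader might infer that the response rule misclassified someone. No patient injected only at elbow or shoulder is documented, and the Protocol separately plans to compare tone at all the affected joints.

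The retained videos and the presented abstract, whose title concerns postures and caregiver burden, show that posture was not ignored. Neither is a quantitative tone outcome.

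**Conclusion.** The point holds in this form. Two of three effects in the objective, and two of five quantitative secondary outcomes, were collected and left unreported, which creates a risk of outcome-reporting bias. The MAS reliability question was known beforehand, and the time reason is applied selectively. No quantitative tone outcome remains for the rigidity part of the primary objective. The carer-burden part keeps its measure.

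This rests on the deviation notes alone, since the manuscript is not at hand. The notes state final reporting decisions, so this is not a mere mismatch between a record of changes and current text. The size and direction of any bias cannot be judged without the data or the date of the decision.

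**What to change.** 1. Report MAS and time to perform care for all patients in both cycles with the planned mixed model, in a supplement labelled with the reliability and carer-variation limits. For time, use the tasks actually timed: nail cutting was dropped from the assessments, so that component may not exist.
2. State when each omission was decided relative to unblinding.
3. Apply the carer-variation caveat to the VAS and the caregiver's Global Assessment, mention it for the Carer Burden Scale, and note its consequence for the dyad random effect.
4. Show MAS response on the injected joints, labelled as post hoc, beside the prespecified wrist-and-finger rule.
5. If MAS stays unreported, limit any primary conclusion to carer burden and make no claim about tone.

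The cost is a few extra tables of noisy data. Both outcomes were collected. The Protocol plans ongoing data entry but does not confirm that these items were entered, so some entry work may remain.

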**DEVIATION OF FINAL MANUSCRIPT FROM PROTOCOL SUBMITTED TO REB**

***This data was collected but it became clear that this method of determining time it takes to accomplish morning routine was not feasible. There were different people performing morning care at each assessment in different ways and with variable efficiency despite trying to ensure prior to emrolment that this was uniform. For “time to perform morning care” to become a valid measure it would be necessary to standardize the protocol for administering care and by the same individual. As this study was a pilot study also looking at feasibility, we recognized that the way we collected this did not provide meaningful and valid data and chose to omit from our reporting. A future study on a larger scale (if performed) would need to consider these factors and record the time variable in a different way.***

1. **Visual Analogue Scale:** A caregiver burden visual analogue scale (VAS) will be completed by the professional caregiver caring for the patient in order to assess perception of ease of caregiving (16). A VAS will be used because it has been found to be valid in capturing subjective perceptions of health-related quality of life and other qualitative health outcomes (24). The VAS consists of a 100 mm line with anchors of 0 “giving care to the residents is very difficult” and 100 “giving care to the residents is very easy”.
2. **Global Assessment**: Overall response to treatment will be evaluated by the study investigator and by the professional caregiver caring for the patient using the global assessment scale (26) at each follow-up visit. A score of -4 indicates very marked worsening, 0 no change, and +4 very marked improvement.
3. **Pain:** As patients with advanced dementia are not able to express their experience of pain, a surrogate measure, the Pain Assessment in Advanced Dementia (PAINAD) Scale (25) will be used by the study nurse at each assessment time point to objectively evaluate correlates of pain and determine whether treatment with Botulinum toxin reduces the discomfort experienced during morning care. The PAINAD scale consists of 5 items (breathing, negative vocalization, facial expression, body language, and consolability) scored on a 0-2 point scale and then summed to arrive at a total score. The score will be averaged over 2 days

*Qualitative Assessments*

In addition to quantitative objective measures to determine reduction in burden, the professional caregiver will be questioned using open-ended interview techniques regarding what they have noted to be the most relevant impact from the intervention. They will be asked to provide any additional observations or comments that may not have been directly addressed by the study outcomes. This will provide insights into possible future research questions to be addressed and may provide possible other relevant outcome measures. The interviews will be carried out at 6 and 22 weeks by the clinical co-ordinator trained in qualitative research methods.

*Videos*

To document visually the impact of injections on postures and skin integrity, all subjects will be videotaped receiving morning care before injections and at each assessment following injections.

*Side Effects*

At each assessment, the professional caregiver will be asked about any adverse-effects they may have noticed as a consequence of the injections. They will be specifically questioned regarding excessive weakness, local skin effects including bruising or hypersensitivity, and distal spread effects such as breathing or swallowing impairment differing from before treatment. Any side-effect attributed to treatment will be monitored and recorded throughout the treatment period. If any serious adverse effects emerge (ie breathing or swallowing difficulty), treatment will be unblinded and appropriate interventions will be effected.

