**Blinding**

Botulinum toxin for injection will be prepared at the pharmacy by diluting Xeomin (Merz GmBH) with 0.9% saline to a concentration of 100 mouse units (MU)/mL. As the solution is colorless and odorless, it is indistinguishable from an equivalent volume of isotonic saline which will be used for the placebo injections. The syringes with solution, either placebo or Botulinum toxin A, will be sent to the Elkie Adler Spasticity Management Clinic labeled with the subject’s code. All the investigators at the Clinic, the subject and the professional caregiver will be blinded to whether a subject received drug or placebo during the entire study. A procedure to break code will be in place at the pharmacy in case of medical emergency.

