**Outcomes**

Assessment of outcomes will occur at baseline/screening, 2, 6, 12 and 16 weeks following injections at baseline and 16 weeks. Week 6 and 22 have been chosen as the primary endpoints, as reduction in tone due to Botulinum toxin should be well established 6 weeks following injections. Cycles of 16 weeks have been chosen as any residual effect of treatment should be worn off by this time (19).

*Outcome measures:*

*Primary Outcome*

1. **Impact on caregiver burden**: Impact on caregiver burden in providing upper extremity care will be measured by the Carer Burden Scale (22, 23). The Carer Burden Scale consists of four items (cleaning the palm, cutting the fingernails, dressing, cleaning under the armpit). Each item will be rated by the study nurse (blinded to treatment allocation) on a five point Likert scale (“no difficulty” to “cannot do task”) at each time point (baseline, weeks 2, 6, 12, and 16 following injections) for a period of 2 days and scores will be averaged. Items scored will be summed and divided by the number of items answered giving a summary carer-burden score (0 = no carer burden 4 = maximum carer burden).

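### Side effects are recorded only if attributed to treatment, by no named role and with no stated criterion, so events judged unrelated are lost in both cycles

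*Protocol*

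**What the plan says.** The protocol's Side Effects section contains four relevant statements, in this order.

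1. The opening question. At each assessment, "the professional caregiver will be asked about any adverse-effects they may have noticed as a consequence of the injections".
2. Directed questions. The caregiver is then asked specifically about excessive weakness, local skin effects, and "distal spread effects such as breathing or swallowing impairment differing from before treatment".
3. The recording rule. "Any side-effect attributed to treatment will be monitored and recorded throughout the treatment period".
4. Serious events. "If any serious adverse effects emerge (ie breathing or swallowing difficulty), treatment will be unblinded and appropriate interventions will be effected".

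Three other places bear on how these work. Under Outcomes, "Assessment of outcomes will occur at baseline/screening, 2, 6, 12 and 16 weeks following injections at baseline and 16 weeks". Under Blinding, the clinic investigators, "the subject and the professional caregiver will be blinded to whether a subject received drug or placebo during the entire study". In the description of the pain outcome, "As patients with advanced dementia are not able to express their experience of pain, a surrogate measure" is used, so caregivers and staff are the practical source of safety information.

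The document gives no other rule for recording adverse events. Safety is not among the objectives listed under Pilot study objectives, and no between-treatment safety analysis is described. The Rationale for Study places proof of safety in a later phase III trial.

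**The concern.** In a blinded placebo-controlled crossover, the placebo cycle shows how often an event occurs without the drug. That works only if events are recorded the same way in both cycles without a prior decision about cause. Here the decision about cause comes first and controls what enters the record.

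In this population an alternative explanation is nearly always available. The Background section names infection and skin breakdown as consequences of fixed postures, and skin breakdown is one of the conditions that can qualify a patient for entry. The Rationale for Study says that side effects are few because the toxin acts locally. A systemic event is therefore one that the study team has a stated reason to call unrelated.

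At stake is how complete the pilot's safety information is. An analysis plan, whatever it says, cannot recover an event that was never written down. The pilot is meant to prepare a phase III trial in which safety is an aim, and finding obstacles to data gathering is one of its own objectives.

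**Working it through.** There is no stated figure to reproduce: the protocol gives no adverse-event rate, safety test or safety sample size. The check is a reading of the text, followed by an illustration on assumed values.

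**Step 1. What each sentence lets through.**

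| Kind of event | Asked about? | Recorded under the rule? |
|---|---|---|
| Serious breathing or swallowing difficulty | Yes, by name | Acted on when it emerges; no attribution condition |
| Milder weakness, local skin effect or distal spread, judged related | Yes, by name | Yes |
| The same, judged unrelated | Yes, by name | Not required |
| Event on no list (e.g. infection, fall), linked to the injections by the caregiver | By the opening question | Yes, if the attribution is accepted |
| Event on no list, not linked to the injections | No | Not required |

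The third and fifth rows are the gap. The distal-spread question compares with the state before treatment and so asks nothing about cause. The filter comes back one sentence later, in the recording rule. No sentence says who makes the attribution or by what criterion.

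**Step 2. Chance that an event type appears in the record at all.** Inputs: n = 10 patients, each receiving both treatments (Participants; Trial design). Assumed, not in the documents: true per-patient risk p in one cycle, and probability a that an event is attributed and so recorded. With independent patients,

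P(at least one recorded) = 1 − (1 − p·a)^10.

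| p | a = 1 (all recorded) | a = 0.75 | a = 0.50 | a = 0.25 |
|---|---|---|---|---|
| 0.10 | 65% | 54% | 40% | 22% |
| 0.20 | 89% | 80% | 65% | 40% |
| 0.30 | 97% | 92% | 80% | 54% |

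Example: p = 0.20, a = 0.50 gives 1 − 0.90^10 = 65%, against 1 − 0.80^10 = 89% with no filter.

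**Step 3. Effect on a difference between treatments when attribution is the same in both cycles.** Recorded difference = a·(p_active − p_placebo). For an assumed 0.30 against 0.10, the true 0.20 becomes 0.15, 0.10 or 0.05 for a = 0.75, 0.50 or 0.25. This is dilution; the sign is unchanged.

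**Step 4. What directional bias would need.** With equal true risk p in both cycles, recorded difference = p·(a_active − a_placebo). For p = 0.20 and attribution of 0.75 against 0.25, this is 0.20 × 0.50 = +0.10; with the two reversed it is −0.10. A false difference therefore needs attribution to differ by treatment, which blinded reporters can produce only by guessing the allocation.

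**The case against.** The strongest reply is that the section does more than filter. The events of most concern with this drug are asked about by name at each assessment, against the pre-treatment state, and serious breathing or swallowing difficulty triggers action whatever its supposed cause. This stands, and it limits the point to milder changes judged unrelated and to events on no list.

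Four stronger readings are tempting and are not supported.

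- A reader might infer that an event is recorded only if the caregiver attributes it. The recording rule names no attributing role. That is a gap in itself, but it does not assign the decision to the caregiver.
- A reader might infer that distal spread is the class most likely to be missed. It is the best protected. It could be lost only if the caregiver does not observe it despite being asked, or if a reported non-serious change is then judged unrelated.
- A reader might infer that the safety comparison is biased. No such comparison is planned in this document, and caregiver and investigators are blinded, so equal attribution is the default expectation. A route to guessing exists, since the caregiver rates global response at each follow-up visit and may notice a change in tone, but nothing in the document shows that it operated.
- A reader might infer from the deviation note on time to perform care ("There were different people performing morning care at each assessment in different ways and with variable efficiency") that the safety informant also changed. That note explains why care times were unusable. It does not say who answered the side-effect questions, and Trial design identifies the professional caregiver as the primary nurse. The 6-week gap between visits is likewise the longest one (weeks 6 to 12); the others are 2, 4 and 4 weeks.

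It is also fair to say that a pilot of 10 patients without a safety objective will not settle safety. That lowers the stakes, but it is no reason to discard events at the point of collection.

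**Conclusion.** The point holds in a limited form. Followed exactly, the rule leaves out adverse events judged unrelated to the injections, in both cycles, by an unnamed decision-maker and on no stated criterion. The expected consequence is under-recording and dilution of any description of active against placebo, not a demonstrated bias in either direction.

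The size is not known. The tables show what the filter would do for risks of 0.10 to 0.30 and attribution of 25% to 100%. Neither range comes from the protocol, and the calculation assumes independent patients and, for dilution, the same attribution in both cycles. This is a cheap improvement to the safety data and does not threaten the primary outcome.

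**What to change.** Change the Side Effects section as follows.

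- Record every new or worsened adverse event at each planned assessment, regardless of suspected cause.
- Remove the causal phrase from the end of the opening question to the caregiver.
- Keep the directed questions on weakness, skin effects and distal spread.
- Have a named role, blinded to allocation, judge causality in a separate field, so that events can be listed by treatment received and cycle with and without that judgement.

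This needs no extra visit and does not touch the rule for serious events. The cost is new wording on the case report form and a longer list containing more unrelated events.

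The deviation notes and the Knowledge translation section show that the pilot has been carried out. For data already collected under this rule, any safety statement should say that it covers only side effects attributed to treatment. The rule should not be carried into the phase III protocol.
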